### 2.6. Outcomes measures

Researchers determined that the following data will be collected to observe the efficacy and safety of the TCM BDT for FC. The detailed research schedule for this registry study is presented in Table 1.

**Table 1 T1:** Research schedule of the registry study.

	Enrollment baseline	Subsequent visits	End of treatment	Subsequent visits
		The 7th day		The 14th day after the end
Informed consent	√			
Eligibility screening	√			
Matters needing attention	√			
Demographic characteristics	√			
Physical examination form	√	√	√	√
Bowel movement dairy (everyday)	√	√	√	√
PAC-SYM	√	√	√	√
PAC-QOL	√	√	√	√
TCM Syndrome Scale*	√	√	√	√
Economic questionnaire			√	
AEs		√	√	√

Note: the time window is specified as 5 days.

AE = adverse events, PAC-QOL = Patient Assessment of Constipation Quality of Life questionnaire, PAC-SYM = Patient Assessment of Constipation Symptoms questionnaire, TCM = traditional Chinese medicine.

* Only for people with dryness-heat syndrome.

Demographic characteristics: Age, sex, occupation, educational background, and medical history were collected as the basic demographic information.Anthropometric data and general condition: Vital signs such as blood pressure, body temperature, rhythm, and pulse rate will be collected as variables related to general health conditions. Data on mental condition, sleep condition, and diet will also be collected as a general condition. These messages will be completed in a physical examination form.Bowel movement: Participants were required to record the bowel movement diary during the treatment period every day, which included frequency, feeling in complete evacuation, and form with Bristol stool scale (ranging from “separate hard lumps” to “watery”).Patient Assessment of Constipation Symptoms questionnaire. A US survey showed that the most frequent symptoms of chronic constipation were straining, hard stools, abdominal discomfort, bloating, infrequent bowel movements, and feeling of incomplete evacuation after bowel movement.^[11]^ Therefore, it is important to have a careful history assessing the presence of these symptoms and their duration and progression, and the Patient Assessment of Constipation Symptoms questionnaire is recommended for the clinical evaluation of patients with constipation.Patient Assessment of Constipation Quality of Life questionnaire.^[12]^ The scoring items were divided into 28 items, and each item was divided into 5 grades according to the degree, with 1, 2, 3, 4, and 5 points. The higher the score, the worse is the quality of life.TCM syndrome scale (only for dryness-heat syndrome). It was used to determine whether the participant belonged to the TCM syndrome of dryness-heat at the beginning of the study. These participants were required to record their TCM syndrome scale again after 14 days of treatment.Time taken for the laxative product to appear again after treatment.Adverse events (AEs): In case of occurrence of any AE, we will immediately provide appropriate treatment to the participant according to the guidelines of the clinic and then observe the participant’s progress during the follow-up visit.Economic indicators: Cost-utility analysis. The economic questionnaire must be completely completed at the end of the treatment.

### 2.7. Data management and quality control

Researchers participating in clinical research must have professional qualifications and abilities, which are determined after a qualification review. The registration observation form was designed according to the study plan and data collection was completed by the clinician. All the collected data were managed using a confidential online database.

To ensure the accuracy of the data, training was performed before the start of the trial. Researchers should have a full understanding of the clinical study protocol and specific connotations of each index. The description of the subjective symptoms of the participants should be objective and should not be induced or prompted. The specified objective indicators were checked according to the time and method specified in the plan. In addition, attention should be paid to the observation of adverse reactions or unexpected toxicity and side effects.

### 2.8. Sample size calculation

We plan to recruit at least 1000 patients during the study period. Empirically considering the trends of patients visiting each community hospital, we estimated that approximately 1000 participants will be enrolled (100 patients or more per year per clinic) for a year. The study started in July 2022, is currently ongoing, and will finish in July 2023.

### 2.9. Statistical analysis plan

All statistical analyses were conducted using two-tailed tests and the significance level was set at 5%. An analysis of covariance will be performed when it is necessary to control for underlying variables, such as demographic variables. The propensity score can effectively balance the distribution and composition of each characteristic variable between groups and evaluate the relationship or role between intervention measures and outcome variables. It is often used to control for confounding bias among non-randomized groups in observational studies. The generalized estimating equation has obvious advantages over other methods for evaluating propensity score values and is the most recommended algorithm among the current evaluation methods for propensity score values.^[13]^ The mean of other scoring data will be analyzed using the *t* test or the chi-square test. The incidence of AEs within the groups was also evaluated using the chi-squared test. For missing data, the last observation carried forward will be used through a case report form inspection to replace the missing value. All statistical analyses in this study were conducted using SPSS 20.0 (SPSS Inc., IBM Corp., Armonk, NY).

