**Figure 1. F1:**
[figure not shown]
Study flow chart. BDT = Besunyen Detox Tea, FC = functional constipation, PAC-QOL = Patient Assessment of Constipation Quality of Life questionnaire, PAC-SYM = Patient Assessment of Constipation Symptoms questionnaire, TCM = traditional Chinese medicine.

The efficacy and safety of BDT in patients with FC has been accurately recorded under real conditions. The natural grouping method was used in this study, and the participants were not divided into groups or queues in advance. They will be divided into a dryness-heat syndrome group and a non-dryness-heat syndrome group by filling out the TCM syndrome scale when entering the study. The laxative efficacy of the two groups will be analyzed from different perspectives.

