### 2.4. Recruitment

Participants will be recruited from 3 comprehensive hospitals and 15 primary medical institutions across China. We will also advertise through websites and post recruitment posters on the walls of the entrance of each clinic to encourage voluntary participation in this study. If the participants met the inclusion criteria in this study, the researcher will fully explain the aim of this study and details of the procedures, including research usage, confidentiality, and provision of data to third parties for analysis, and will obtain informed consent from the potential participants. Simultaneously, professional clinicians will be arranged to observe the status of the participants and provide medical assistance.

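### The comparison of BDT's effect between non-randomised syndrome groups is not tied to the baseline score: the named test is unadjusted, covariance adjustment is conditional, and propensity-score use is not committed to.

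*Protocol article*

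**What the plan says.** The Introduction sets as an aim the comparison of BDT's effect between patients with and without dryness-heat syndrome. All participants take BDT. Section 2.1 (text under Figure 1) makes clear that the groups are not assigned: "The natural grouping method was used in this study, and the participants were not divided into groups or queues in advance". It adds: "They will be divided into a dryness-heat syndrome group and a non-dryness-heat syndrome group by filling out the TCM syndrome scale when entering the study".

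Section 2.9 then says three things that bear on how scores are compared:

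- Covariance analysis: "An analysis of covariance will be performed when it is necessary to control for underlying variables, such as demographic variables". No trigger for necessity is given.
- Propensity score: described in general terms as a way to balance characteristics and control confounding in non-randomised groups, with a remark on the preferred estimating algorithm. No sentence says that it will be used, with which covariates, in what way, or for which outcome.
- Other scores: "The mean of other scoring data will be analyzed using the" t test or chi-square test.

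Table 1 (section 2.6) schedules PAC-SYM and PAC-QOL at enrolment and at every later visit, so each participant's own starting score is due to be collected. The Discussion lists severity of constipation among the factors to be analysed for their influence on efficacy, but does not link this to the syndrome comparison.

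**The concern.** The groups are defined by a symptom-based scale at entry, so there is no design reason for them to start level on constipation symptoms or quality of life. In a randomised comparison a baseline gap is chance. Here it may be systematic, and a larger sample does not remove it.

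Suppose follow-up means are compared without using the starting score. If dryness-heat participants start worse, an equal response can look like a poorer effect and a better response can be hidden. If they start better, the reverse holds. The comparison is meant to support the study's claim about matching a product to a syndrome, so a starting difference mistaken for a difference in effect would go to that claim. A decision on adjustment left until the data are in hand also leaves the result open to the choice made then.

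**Working it through.** **The plan's own figures.** Section 2.9: "All statistical analyses were conducted using two-tailed tests and the significance level was set at 5" percent. Section 2.8: "We plan to recruit at least 1000 patients during the study period". That total rests on accrual, not power: "approximately 1000 participants will be enrolled (100 patients or more per year per clinic) for a year". It does not reproduce from the site counts: 15 × 100 = 1500 and 18 × 100 = 1800, and only 10 clinics at 100 would give 1000. This point does not depend on that mismatch; 1000 is used as the total.

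**Assumptions (none is in the document).** Entry gap d in SD units; baseline-to-follow-up correlation r; SD of 1 at both times; group splits of 500/500, 300/700 and 200/800; no true syndrome effect.

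**Formulas.** For a test whose expected difference is δ and standard error is SE, two-sided rejection at 5% is Φ(|δ|/SE − 1.96) + Φ(−|δ|/SE − 1.96). For a t test of follow-up means, SE = √(1/n1 + 1/n2), which is 0.0632, 0.0690 and 0.0791 for the three splits.

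No syndrome effect can mean two different things:

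- Model A: follow-up depends on baseline and not on group. The follow-up difference is r·d.
- Model B: both groups change equally. The follow-up difference is d.

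**Unadjusted t test of follow-up means, 500/500.**

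- A, r = 0.5, d = 0.2: 0.10/0.0632 = 1.58, rejection 35%.
- A, r = 0.5, d = 0.3: 0.15/0.0632 = 2.37, rejection 66%.
- B, d = 0.2: 0.20/0.0632 = 3.16, rejection 88.5%.
- B, d = 0.3: 0.30/0.0632 = 4.74, rejection 99.7%.
- d = 0: rejection 5% under either model.

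**Sensitivity to the assumptions.**

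| Split | Model | d = 0.1 | d = 0.2 | d = 0.3 |
|---|---|---|---|---|
| 500/500 | A, r = 0.3 | 7.6% | 15.8% | 29.6% |
| 500/500 | A, r = 0.5 | 12.4% | 35.3% | 66.0% |
| 500/500 | A, r = 0.7 | 19.8% | 60.0% | 91.3% |
| 300/700 | A, r = 0.5 | 11.2% | 30.5% | 58.5% |
| 200/800 | A, r = 0.5 | 9.7% | 24.4% | 47.5% |
| 500/500 | B | 35.3% | 88.5% | 99.7% |
| 300/700 | B | 30.5% | 82.6% | 99.2% |
| 200/800 | B | 24.4% | 71.6% | 96.7% |

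In simulation under A with r = 0.5 (2,000 runs, 500/500), adjusting only for a covariate unrelated to the score left the rate at 36% (d = 0.2) and 64% (d = 0.3). Demographic adjustment alone therefore need not help.

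**Do the baseline-using analyses repair this?** Each does so under one model only.

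- Covariance analysis on the baseline score. Under A its expected group difference is 0; simulated rejection was 4.2% to 5.7% over d = 0.2 to 0.5 at 500/500 and 300/700. Under B it is d − r·d = (1 − r)·d. With d = 0.3 and r = 0.5 that is 0.15, against SE ≈ √(1 − 0.25) × 0.0632 = 0.0548, ratio 2.74, rejection about 78% (77% in simulation with 4,000 runs; 44% at d = 0.2; 15% at d = 0.1).
- Change-from-baseline t test. Under B its expected difference is 0 and it holds 5%. Under A it is −(1 − r)·d, with SD of change √(2 − 2r) = 1 at r = 0.5. With d = 0.2 the ratio is 0.10/0.0632 = 1.58, rejection 35%; with d = 0.3, 66%.

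The two estimates differ by (1 − r)·d, for example 0.15 SD at d = 0.3 and r = 0.5. Each errs where the other is right, and the data cannot say which model is true.

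**The case against.** Several stronger readings are tempting, and the document does not support them.

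- *The plan compares raw post-treatment means of PAC-SYM and PAC-QOL.* Section 2.9 does not name these scales in the t-test sentence, and does not say whether the mean is a follow-up value or a change. The word for remaining scores could mean those not already handled by covariance or propensity methods. This stands, so the bias can be stated only as a possibility.
- *Adjustment is limited to demographic variables.* They are given as an example, and the Discussion names severity of constipation as a factor for efficacy. A baseline score is not excluded; it is just not fixed.
- *Confounding was overlooked.* The propensity-score sentences show that it was considered. They do not commit to a use, a covariate list or an outcome, so they do not settle the matter.
- *A starting difference will be read as a drug effect.* That needs an entry gap, an unadjusted test of follow-up values and no other adjustment, all together.
- *Covariance analysis restores 5%.* Only if follow-up depends on baseline alone. If both groups change equally, it fails and the change score succeeds.

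A further objection is that an article may leave model detail to a full plan. That holds for a covariate list. It does not cover what the article itself states: an adjustment made conditional without a trigger, and an unadjusted test as the named method, in a comparison of self-formed groups.

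**Conclusion.** The concern holds in a limited form. The article does not fix whether or how the syndrome comparison uses the baseline score, and the methods that it does name allow an unadjusted comparison. If the groups differ at entry and follow-up means are compared unadjusted, false rejection at 500/500 and correlation 0.5 is 35% to 66% for a gap of 0.2 to 0.3 SD when follow-up depends only on baseline, and 88.5% to 99.7% when both groups change equally. The gap, correlation and split are assumptions, and without a gap there is no inflation. The figures show how sensitive a study of 1000 would be; they do not predict its result. Because no single analysis is valid under both models, the remedy is to show two with their assumptions. The change should be made, but nothing here shows that the comparison must fail.

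**What to change.** In section 2.9:

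1. Remove the condition on covariance analysis. For the syndrome comparison of PAC-SYM and PAC-QOL, prespecify a model that always includes that score's own baseline value and the demographic covariates.
2. Report the change-from-baseline difference beside it, both with 95% confidence intervals.
3. State that the two rest on different untestable assumptions in non-randomised groups: for covariance analysis, that follow-up depends on baseline and not on group; for the change score, that both groups would change equally. Draw a conclusion about syndrome only where the two agree, and define agreement in advance.
4. If the propensity score is used, include the baseline score in it and say how it is applied. If it is not, delete the passage.

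The cost is a few sentences and a little more analysis. Both scores are already scheduled at baseline, and covariance analysis is already named. The downside is a less definite conclusion if the two analyses disagree.

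### GEE is recommended for the propensity score, where it adds practically nothing over logistic regression, while no stated outcome method uses the repeated visits or the site

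*Protocol article*

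**What the plan says.** Section 2.9 of the protocol article describes the propensity score as the tool against confounding between non-randomised groups, then adds "The generalized estimating equation has obvious advantages over other methods for evaluating propensity score values and is the most recommended algorithm". GEE is named nowhere else.

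For outcomes, the section offers two routes. One is conditional: "An analysis of covariance will be performed when it is necessary to control for underlying variables, such as demographic variables". The other is general: "The mean of other scoring data will be analyzed using" a t test or a chi-square test. For safety it states "The incidence of AEs within the groups was also evaluated using the chi-squared test". Testing is two-sided at 5%.

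The data structure is given elsewhere:

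- The text after Figure 1 (section 2.1) forms the dryness-heat and non-dryness-heat groups from the syndrome scale completed at entry.
- Table 1 (section 2.6) schedules PAC-SYM and PAC-QOL at baseline, day 7, end of treatment and 14 days after the end. The bowel diary is daily.
- On sites, section 2.4 says "Participants will be recruited from 3 comprehensive hospitals and 15 primary medical institutions across China".

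**The concern.** GEE is built for correlated responses. The propensity model's response is a label fixed once per participant. Table 1 repeats the syndrome scale later in dryness-heat participants, but that does not change the group formed at entry. So the one method in the plan designed for correlated data is attached to the one variable that has no within-participant correlation. The outcomes that are correlated, across visits and possibly within sites, have no stated method that uses that structure. The sentence on means is also loose, because a chi-square test does not compare means.

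The syndrome comparison is a declared aim (Introduction and Discussion) and is not randomised. Its credibility rests on confounding control and on sound standard errors. A reader who trusts the stated advantage of GEE may think that differences between sites have been dealt with when they have not.

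**Working it through.** The plan gives no figure of its own to reproduce on this point.

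**Inputs from the article.** 1000 participants (section 2.8); 3 + 15 = 18 sites, so m = 1000/18 = 55.6 per site; two-sided 5% (section 2.9); one baseline visit and three later visits for PAC-SYM and PAC-QOL (Table 1).

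**Assumed, because the article gives none.** Outcome intraclass correlation by site (ICC_y) 0.01 to 0.10; syndrome-label intraclass correlation by site (ICC_x) 0 to 0.10; correlation between visits 0.3 to 0.7; half the participants in each syndrome group.

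**Step 1. Propensity score by GEE or by logistic regression** (60 simulated data sets per setting, ICC_x on the logit scale).

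- One record per participant, clustered on participant: the largest difference from the logistic score is 3e-16. The two are the same model.
- Clustered by site with exchangeable correlation: mean correlation with the logistic score above 0.998; mean absolute difference 0.001 to 0.006.
- Imbalance in the site effect after weighting, as a standardised difference at ICC_x 0.05: logistic 0.389, GEE 0.390, logistic with site as a covariate 0.011. At ICC_x 0.10: 0.518, 0.519 and 0.018.

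GEE neither changes the score materially nor balances sites. Putting site in the model does.

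**Step 2. t test with visits pooled as if independent.** With three later visits and visit correlation r, the variance ratio is VR = 1 + (3 − 1)r, and the true error is 2[1 − Φ(1.96/√VR)].

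- r = 0.3: VR = 1.6, error 12.1%
- r = 0.5: VR = 2.0, error 16.6% (simulated 16.0%)
- r = 0.7: VR = 2.4, error 20.6%

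**Step 3. t test at one visit, ignoring site.** VR = 1 + (m − 1) × ICC_x × ICC_y. For example, 1 + 54.6 × 0.05 × 0.05 = 1.136. Simulation used 18 sites and 3000 runs; its standard error near 5% is √(0.05 × 0.95/3000) = 0.4 percentage points.

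| ICC_y | ICC_x | VR | Error, formula | Error, simulated | Simulated, site in model |
|---|---|---|---|---|---|
| 0.01 | 0.05 | 1.027 | 5.3% | 5.4% | 5.1% |
| 0.05 | 0 | 1.000 | 5.0% | 5.1% | 4.9% |
| 0.05 | 0.05 | 1.136 | 6.6% | 6.5% | 5.5% |
| 0.05 | 0.10 | 1.273 | 8.2% | 8.1% | 5.4% |
| 0.10 | 0.05 | 1.273 | 8.2% | 7.6% | 4.9% |
| 0.10 | 0.10 | 1.546 | 11.5% | 11.2% | 5.3% |

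If the syndrome share is identical at every site, VR = 1 − ICC_y, that is 0.99 to 0.90, and the test is slightly conservative (4.9% to 3.9%).

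**Step 4. Precision.** Where a single-visit t test is valid, adjusting for a baseline value correlated r with the outcome multiplies the residual variance by 1 − r². Over the same assumed range this is 1 − 0.09 = 0.91 to 1 − 0.49 = 0.51, taking the groups to have similar baseline means.

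**The case against.** The strongest reply is that the article is condensed. The visit analysed, the repeated-measures model and the handling of site may sit in a full protocol or analysis plan that is not shown, and their absence alone would be no finding. That stands. This point therefore rests on what section 2.9 does state: a preference for GEE where it has no practical advantage, and tests for the scores that use neither visit nor site.

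Other parts of the defence also stand:

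- A reader might infer that outcomes get only unadjusted tests and that baseline is ignored altogether. The article does not support this. It names ANCOVA and a propensity score, and the Discussion plans an analysis of factors that include constipation severity. No sentence assigns PAC-SYM or PAC-QOL by name to a t test; they fall under the general sentence on scoring data. ANCOVA remains conditional, however, and as described it does not address visits or site.
- A reader might infer that the adverse-event test is undefined, because Table 1 collects no events at baseline. The natural reading is incidence in each syndrome group, compared between groups. The wording needs tidying; the test exists.
- The GEE sentence does little numerical harm, since the scores are nearly identical to logistic ones. The harm lies in relying on a benefit that is absent.
- Offering a t test or a chi-square test may simply mean choosing by type of data. If so, the article should say so.

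**Conclusion.** The claim made for GEE is unfounded in this design. With one baseline label per participant it gives essentially the logistic score and leaves imbalance between sites unchanged. No stated outcome method uses the four visits or the 18 sites.

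It is tempting to conclude that the standard errors of the syndrome comparison are wrong. The article does not support that as a certainty. It nowhere says that visits are pooled, and it gives no information on how syndrome share or outcome varies by site. The conclusion is conditional: about 12% to 21% true error if three visits are pooled (assumed visit correlation 0.3 to 0.7, no site clustering); about 6.5% to 11% for a single-visit test if both intraclass correlations lie between 0.05 and 0.10; about 5% if the syndrome share does not vary by site. In that last case a single-visit t test is valid, but less precise than a baseline-adjusted model. All these sizes rest on assumed correlations.

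**What to change.** Revise section 2.9 as follows.

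- Delete the statement that GEE is the preferred way to obtain propensity scores. Estimate the score by logistic regression of dryness-heat status on baseline covariates (age, sex, occupation, education, medical history), baseline PAC-SYM and site.
- Analyse PAC-SYM, PAC-QOL and diary scores with a linear mixed model, or with GEE clustered on participant, containing baseline value, syndrome group, visit, group-by-visit and site. Including site as a covariate avoids clustering on only 18 units, which would need a small-sample correction. State how this model sits with the present rule that "For missing data, the last observation carried forward will be used".
- Keep the chi-square test for categorical outcomes only.
- Word the adverse-event test as a comparison of incidence between the two syndrome groups.

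The cost is rewording and slightly more analysis work. No new data are needed: the covariates, scores and visits are already scheduled, and site is known for every participant.

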## 2. Participants and Methods

### 2.1. Study design

The aim of the proposed study was to conduct a multicenter, prospective, observational registry study with 1000 participants who were diagnosed with FC (Fig. 1). The diagnosis of FC was based on the Rome IV criteria. Participants who voluntarily signed a written informed consent form after receiving sufficient explanation of the benefits and risks of participating in the study will be evaluated for compliance with the inclusion and exclusion criteria through a screening process on their first visit. After screening, eligible participants were assigned to the registry. BDT will undergo for 2 weeks and there will be 2 weeks of follow-up after the treatment. Participants could stop taking the BDT if FC was relieved after continuous treatment for at least 7 days.

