### 2.5. Exposure

The participants will receive treatment with BDT (Beijing Aote Shuer Health Care Product Development Co. Ltd, Lot Number: 01200703, Beijing, China) twice a day (1 hour after lunch and 1 hour after dinner). The specification of tea is 2.5g/bag, and it is brewed once with 150 to 250 mL of boiling water. Health food and drugs (including dietary fiber and probiotics) with laxative effects shall not be taken orally and externally 4 weeks before the trial and during the trail, which will affect the judgment of the results.

During the experiment, the diet, drinking water, exercise, and rest were basically the same as before. If the constipation is aggravated, it is recommended that the participant go to the hospital for physical examination and use other laxative drugs. In case of serious adverse reactions, the participant shall immediately stop taking this product and seek medical treatment in time. The trial unit will bear the treatment costs and corresponding compensation arising therefrom.

The compliance of the participants was monitored by the counting method of the test products. Compliance = (actual dose/expected dose) × 100%.

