## 3. Discussion

This paper describes the protocol of a multicenter, prospective, registry-based observational registry study to monitor the efficacy and safety of the TCM BDT for FC. BDT is a functional food for Chinese herbal tea bags, which has a laxative effect and has been commonly used among people with constipation for more than 20 years in China. In particular, the active ingredients of BDT, such as total anthraquinones, sennoside A, sennoside B, and rhein, are the main compounds of BDT in the treatment of constipation. Previous studies have demonstrated that anthraquinone, especially its dianthrone compounds, such as sennoside A and sennoside B, exert significant laxative effects in promoting gastrointestinal motility and relieving FC.^[14]^

There are a large number of TCM health foods in China, but the guiding principles for the use of TCM health foods are currently lacking. In order to maximize the effect of TCM health foods on the importance of the application of TCM syndrome differentiation to health products, we put the standard of syndrome differentiation into the design of this study. As we know, TCM has its own properties (such as hot or cold), and it is theoretically believed that BDT has a better effect on constipation patients with dryness-heat syndrome. We aimed to identify the most suitable syndrome or clinical manifestation of BDT in this study.

This study is the first registry-based study to collect real-world data of participants diagnosed with FC receiving BDT treatment in community hospitals. The results of this registry may demonstrate the acceptance of BDT in patients and evaluate the effectiveness and safety of BDT for FC. Second, the long-term effect of BDT on FC was evaluated by observing the time the participants used the laxative product within 2 weeks of the end of the trial. Furthermore, the laxative effect of BDT on people with different syndromes (dryness-heat syndrome and non-dryness-heat syndrome) was investigated. The factors that affect the efficacy of BDT are analyzed by multiple factors, such as the severity of constipation, age, sex, occupation, and medical history. Finally, we evaluate the economic value of BDT. This is the first study to evaluate the effectiveness of TCM health products that are already on the market for people with different syndromes. This study has great significance.

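### Unrestricted last observation carried forward puts a normally on-treatment value into a missed post-treatment visit, and is likely to overstate sustained benefit if relief wanes after BDT stops

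*Protocol article*

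**What the plan says.** All references are to the protocol article.

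- **Missing data (section 2.9).** "For missing data, the last observation carried forward will be used through a case report form inspection to replace the missing value". This is the only missing-data rule in the article. It is not restricted by outcome, visit or reason for missingness.
- **Timeline (section 2.1).** "BDT will undergo for 2 weeks and there will be 2 weeks of follow-up after the treatment". In addition, "Participants could stop taking the BDT if FC was relieved after continuous treatment for at least 7 days".
- **Visits (section 2.6, Table 1).** PAC-SYM, PAC-QOL and the daily diary are ticked at baseline, day 7, end of treatment and "The 14th day after the end". A note adds: "Note: the time window is specified as 5 days".
- **Diary (section 2.6, text).** "Participants were required to record the bowel movement diary during the treatment period every day". Table 1 ticks the diary at the post-treatment visit as well.
- **Worsening (section 2.5).** If constipation is aggravated, "it is recommended that the participant go to the hospital for physical examination and use other laxative drugs".
- **Purpose of the follow-up (section 3).** "the long-term effect of BDT on FC was evaluated by observing the time the participants used the laxative product within 2 weeks of the end".
- **Comparison (section 2.1).** All participants receive BDT. The groups compared are dryness-heat and non-dryness-heat syndrome, classified at entry.

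**The concern.** Carrying a value forward is an assumption that nothing changes after the last observation. Within the treatment period that may be tolerable. Across the end of treatment it is not neutral, because the product has been withdrawn and the follow-up asks whether the effect lasts. A missed post-treatment visit filled with the end-of-treatment score answers that question by assumption.

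There is no untreated arm. A bias in the before-after change therefore passes straight into the effectiveness estimate, with no control group in which it could cancel. In the syndrome comparison, unequal missingness between the groups could produce a difference where none exists. Values filled in this way and then analysed as observed also make the estimate look more precise than it is.

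**Working it through.** **What the documents supply.** A planned sample of at least 1000 (section 2.8), two-sided 5% tests (section 2.9) and the visit schedule (Table 1). They give no missing rate, SD, effect size or expected course after BDT stops. There is no plan figure to reproduce, and everything below is illustrative.

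**Which value is carried.** The last scheduled visit before the post-treatment one is the end of treatment. If the 5-day window allows an early visit, the post-treatment visit still falls 14 − 5 = 9 days after the end. The carried value is therefore not a near-simultaneous substitute. It is normally, though not always, an on-treatment value: someone who stops at day 7 and is seen at day 14 has already been off BDT for 7 days.

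**Bias in the mean post-treatment improvement.**

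Bias = π · m_rel · (1 − r) · I − (1 − π) · m_non · g

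Here π is the share relieved, I their on-treatment improvement, and r the fraction of it retained off treatment. m_rel and m_non are the shares missing the visit among relieved and non-relieved participants, and g is the later gain of the non-relieved. Assumed: π = 0.5, I = 1.0 SD.

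| Scenario | Calculation | Bias (SD) |
|---|---|---|
| No missing data | all m = 0 | 0 |
| Benefit fully lost (r = 0), g = 0, m_rel = 10% | 0.5 × 0.1 × 1 × 1 | +0.05 |
| Benefit fully lost, g = 0, m_rel = 30% | 0.5 × 0.3 × 1 × 1 | +0.15 |
| Half retained (r = 0.5), g = 0, m_rel = 10% | 0.5 × 0.1 × 0.5 × 1 | +0.025 |
| Half retained, g = 0, m_rel = 30% | 0.5 × 0.3 × 0.5 × 1 | +0.075 |
| Fully retained (r = 1), g = 0 | (1 − r) = 0 | 0 |
| Reverse case: m_rel = 10%, m_non = 30%, g = 0.3, r = 0 | 0.050 − 0.045 | +0.005 |
| Reverse case, r = 0.5 | 0.025 − 0.045 | −0.020 |
| Reverse case, r = 1 | 0 − 0.045 | −0.045 |

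For scale, the standard error of a one-group mean change with SD 1 and n = 1000 is 1/√1000 = 0.032 SD. A bias of 0.05 SD is about 1.6 of these, and 0.15 SD about 4.7.

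**Syndrome comparison.** Assume no true difference, 500 per group, SD 1, π = 0.5, I = 1.0 SD and r = 0. The false difference is 0.5 × (m_A − m_B), where m_A and m_B are the missing shares among relieved participants in each group. The standard error is √(2/500) = 0.063 SD.

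- Equal missingness: false difference 0, rejection at the nominal 5%.
- 20% versus 10%: false difference 0.05 SD, rejection about 12%.
- 30% versus 10%: false difference 0.10 SD, rejection about 35%.
- With a 300/700 split, the last two become about 11% and 31%.

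The sign follows whichever group has more missing values.

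**Standard error.** If imputed values count as observed and have similar spread, the nominal standard error relative to that from the observed values alone is √(1 − m). This is 0.95, 0.89 and 0.84 at m = 10%, 20% and 30%. At 20% it is about 11% too small, whichever way the bias runs.

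**The case against.** The strongest reply is that the rule acts only where a value is absent, and the documents do not show that many will be absent or who they will be. That is correct, and it rules out several stronger readings that a reader might infer.

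- **That early stoppers are missing by design and are filled with their best day.** Section 2.1 lets relieved participants stop taking BDT. It does not let them skip visits or the diary, and Table 1 makes no exception for them. The treatment period in section 2.6 can equally mean the planned two weeks. The value carried would be the last one, not the best.
- **That participants who worsen keep a flattering earlier value.** Section 2.5 does not say that they leave. If they leave after the worsening has been recorded, a poor value is carried, which works against BDT.
- **That a blank diary day inherits an earlier stool count and hides a day without a stool.** Nothing in the article says what a blank day means, or that the rule is run day by day.
- **That every estimate is biased toward BDT.** The syndrome comparison can be biased either way or not at all. The economic questionnaire is collected once, so it has no earlier value to carry.

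It is also fair that a condensed article may leave sensitivity analyses to a fuller plan, so their absence is not held against it. What remains is the rule that the article does state. As written it covers the post-treatment visit, and there it assumes that the effect persists.

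**Conclusion.** The point holds in conditional form. For the visit 14 days after the end of treatment, the rule in section 2.9 is badly chosen because it imposes persistence of effect. Overstated sustained benefit is the likely direction if relief wanes and relieved participants are among those who miss the visit. The bias disappears with complete data or full retention, and can turn negative if poor responders drop out and later improve.

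Under the stated assumptions the main scenarios give 0 to +0.15 SD and the reverse case −0.045 to +0.005 SD. In the syndrome comparison the bias has no fixed direction and is nil in the equal-missingness scenario. The understated standard error applies in either direction of bias. None of these sizes is a forecast, since the missing rate, the off-treatment course and the SD are all assumed.

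The two statements of the diary period in section 2.6 also need reconciling. If the text governs, post-treatment diary values would be absent for everyone, and the rule read literally would fill them from treatment days. If Table 1 governs, they are collected.

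**What to change.** In section 2.9, replace last observation carried forward with the following.

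1. **PAC-SYM and PAC-QOL:** a mixed model for repeated measures on all observed values (baseline, day 7, end of treatment, 14 days after the end), reporting the end-of-treatment and post-treatment visits separately. The model assumes that missingness is explained by the observed data. Add multiple imputation using stop status and reason for stopping as a sensitivity analysis.
2. **Post-treatment visit:** state that no end-of-treatment value is carried into it.
3. **Diary outcomes:** rates over recorded days.
4. **Time to laxative use after treatment:** a censored time, ending at last contact if no use has been recorded.
5. **Diary period:** reconcile the text of section 2.6 with Table 1.

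No responder rule is needed, because the article defines no responder outcome. Nothing here takes a view on the early-stop or other-laxative provisions.

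The cost is slightly more analysis work and a post-treatment estimate that may look less favourable. Items 1 to 4 change the analysis only. Item 5 could affect data collection in a study that section 2.8 describes as already under way, so it should be settled promptly.
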